## Abstract

**Background:**

A previous study has shown similar factors in dyslipidemias (DL) and osteoporosis (OP). However, no cohort study has been reported on the association between DL and OP in the postmenopausal population in China. This study aims to provide epidemiological and pathophysiological evidence regarding the association between DL and bone mass and fracture risk.

**Methods:**

This is a multicenter, prospective cohort study that will have approximately 1,100 representative participants enrolled from multiple hospitals or communities in China. They will be divided into two groups according to whether or not they are exposed to dyslipidemia and will be epidemiologically investigated. Each participant will be visited continuously once every year with a minimum follow-up of 3 years to track incidences of OP. Meanwhile, free bone density screening, questionnaires, and blood sample collection will also be completed during this period.

**Conclusion:**

The current study is likely to provide greater insight into the relationship between lipid metabolism and bone metabolism in postmenopausal women. Furthermore, the research result maybe fed into public health strategies with regard to metabolic disease prevention.

## Introduction

Osteoporosis (OP) is an escalating public health issue that affects more than 200 million people worldwide, with an increasing prevalence in elderly people (1). According to Chinese authoritative data, OP has become an important health problem for people over 50 years old in China, and the problem of OP is particularly serious in middle-aged and elderly women. About 32.0% of people over 65 years old have OP prevalence, of which 10.7% are men and 51.6% are women (2). Dyslipidemias, including a wide range of disorders in lipoprotein metabolism, constitute one of the leading causes of atherosclerotic cardiovascular disease worldwide (3). In addition, patients suffering from DL have an increased risk of metabolic syndrome and obesity (4), which are important causes of premature death and decreased disability-adjusted life-years (DALYs) worldwide (5).

From 2017 to 2020, we conducted the community-based OP and associated fractures screening in the Beijing area (BEYOND study) in order to explore the prevalence of disease, risk factors, and the characteristics of related biomarkers (6, 7). In this study, we found that leptin appears to be a key biomarker associated with PMOP and in combination with other indicators can predict the occurrence of PMOP, suggesting a potential association between lipid metabolism-related indicators and OP (8). Given the worldwide increased body mass index (BMI) and exponentially growing obesity rate, understanding the risk of osteoporosis in the DL population has never been more important (9). Furthermore, recent studies have also increasingly provided evidence of a strong relationship between dyslipidemia and osteoporosis (10, 11). It is suggested that every osteoporotic patient should be screened for dyslipidemia (12).

A previous study has shown similar factors in DL and OP such as lifestyle, inheritance, metabolism, nutrition, and hormone (13). To the best of our knowledge, no cohort study has been reported on the association between DL and OP in the postmenopausal population in China. Hence, a sequential exploration of the deeper causal relationship between DL and OP can provide new evidence for the co-management of these two diseases. We further designed the multicenter prospective study called “DyslipidemIA and risk of osteoporosis in postMenopausal population: a multicenter, prospective cohort stuDy (DIAMOND study),” to provide epidemiological and pathophysiological evidence regarding the association between DL and bone mass and fracture risk. On the contrary, we still keep the expectation that this study will provide the latest evidence for the research of different metabolic diseases.

## Methods

### Study design and settings

The multicenter, prospective cohort study aims to explore the clinical associations between the DL and OP in Chinese postmenopausal women. Data will be collected from a representative sample and the participants will be recruited from multiple hospitals and communities in China. Then, the subjects will be divided into two groups according to whether there is dyslipidemia or not, and an epidemiological investigation will be conducted.

Each participant will be visited continuously once every year with a minimum follow-up of 3 years to track incidences of OP. Furthermore, BMD screening and biological samples will also be gathered. The questionnaire will be administered to collect information about personal characteristics such as health status and potential risks. Important information including the incidence of OP and/or fracture and medication use will be confirmed annually during the follow-up period. The required sample size will be at least 1,100 patients based on a power analysis. A flow chart of the research process is shown in Figure 1.

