Our study has highlighted the scope for inclusion of multicenter, which enables these results, can be extrapolated effectively to other areas. To our knowledge, it is a large population-based longitudinal cohort study for this purpose in China. Besides, the current cohort will not only focus on traditional lifestyle-related and sociodemographic factors, but also conduct comprehensively research on important comorbidities, medication management, risk of fracture, etc. Another feature is the integration of clinical information, BMD assessment, and serum marker test. Through the observation of long-term follow-up, the dynamic change of bone and bone turnover markers are recorded completely. Most important of all, the potential causal relationship and the effect of DL on bone metabolism may be objectively evaluated.

However, there are several limitations in our cohort study. First, the survey sites and the participants will not be randomly chosen. This is mainly because the units with various regions and the basis for cooperation will be considered in this study to better elucidate the pathogenic mechanism of DL and OP. Moreover, this cohort study is more concerned with the proportion of participants who could be followed up. Thus, we will choose stable communities, hospitals, and participants to ensure a greater follow-up rate. Second, the combined disease surveys in the questionnaire may be biased as a result of the self-reported data, especially not inaccessible through electronic medical records.

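### The cohort is called representative and population-based, with results that extrapolate, but the stated selection of sites and women is non-random and favours stability

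*Protocol article*

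**What the plan says.** Four statements claim generality:

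- Abstract, Methods: "approximately 1,100 representative participants enrolled from multiple hospitals or communities in China".
- Study design and settings: "Data will be collected from a representative sample and the participants will be recruited from multiple hospitals and communities in China".
- Discussion, strengths: "it is a large population-based longitudinal cohort study for this purpose in China".
- Discussion, strengths, on the multicenter scope: "which enables these results, can be extrapolated effectively to other areas".

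Three statements, all in the limitations paragraph of the Discussion, describe how selection works:

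- "the survey sites and the participants will not be randomly chosen".
- On the reason: "the units with various regions and the basis for cooperation will be considered in this study".
- On retention: "we will choose stable communities, hospitals, and participants to ensure a greater follow-up rate".

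The Participants section adds that recruitment is spread over the north, south and centre of mainland China, to limit bias from socioeconomic differences.

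**The concern.** A reader of the Abstract or Methods learns only that the sample is representative. The selection process appears late in the Discussion, after the extrapolation claim, and does not change that claim. The two descriptions are not reconciled.

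What is at stake is the reading of the primary outcome. Outcomes of interest names OP incidence as primary, and Statistical analysis says it will be counted in the two groups. If the sample is labelled representative, those group figures will be taken as incidence among Chinese postmenopausal women with and without dyslipidemia. Women chosen because they are likely to stay in follow-up may differ from others in work, education and economic circumstances. These are the factors that the Participants section wants to guard against. The Conclusion also hopes that results will inform public health strategy, where population incidence and a within-cohort association are used differently.

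**Working it through.** The contradiction is textual, so the main check sets the statements side by side.

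1. **What the labels require.** Representative and population-based imply that the women enrolled stand for a defined population, through the sampling method or through later weighting. The article gives no such basis. Its stated ground for extrapolation is that the study has several centres.

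2. **What the design does.** Neither sites nor women are selected at random. Three criteria are named: region, basis for cooperation, and stability. Stability is applied to communities, hospitals and participants, so it acts at both the site and the individual level.

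3. **Whether regional spread closes the gap.** It widens geographic coverage. It does not undo selection on stability, which acts inside each region. Women less likely to remain in follow-up are under-represented in the north, the south and the centre alike.

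4. **Whether the limitation closes the gap.** It discloses the selection openly and gives reasons. It does not qualify the word used in the Abstract and Methods, and it follows the extrapolation claim without withdrawing it.

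5. **Whether the planned numbers are affected.** Inputs from Sample size calculation: 12% without and 20% with dyslipidemia, two-sided 5% level, 90% power, 20% dropout, equal groups. With p̄ = (0.12 + 0.20)/2 = 0.16:

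   n = [1.960·√(2·0.16·0.84) + 1.282·√(0.12·0.88 + 0.20·0.80)]² / 0.08²

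   This rounds up to 440 per group. Allowing for dropout, 440/(1 − 0.20) = 550 per group, or 1,100 in total. This is the article's figure exactly, and power with 440 evaluable women per group is 90.0%. The calculation concerns precision for a two-group contrast. It neither supports nor weakens a claim of representativeness, and the point does not disturb it.

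**The case against.** The strongest reply is that the authors disclose non-random selection as their first limitation and explain it, so nobody who reads the whole article is misled. The study's aim is association, and a comparison of women with and without dyslipidemia does not need a random sample to be valid, or even to be carried to other settings. The public health sentence is hedged. Recruitment was deliberately spread over three regions. This is a condensed article, so the site selection procedure may be set out in a full protocol that is not shown.

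Much of this stands. The fault is unreconciled wording and not concealment, stability is not the only criterion, and non-random recruitment does not by itself undermine the internal comparison. The reply does not rescue the labels, because the Abstract, Methods and extrapolation statements remain unqualified. Nor does the point depend on missing detail: the article itself says that selection is non-random and favours stability.

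Two stronger readings are tempting and should not be made.

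- **The split is fixed at 550:550, so the pooled cohort cannot mirror the population.** The article gives 550 and 550 as a minimum for power. Study design and settings asks for at least 1,100 and has women recruited and then divided by dyslipidemia status. No quota or fixed ratio is stated.
- **A pooled incidence from this cohort would mislead.** No pooled figure is planned; incidence is to be counted in the two groups. Any numerical example would need a population share of dyslipidemia that the article does not give, and would have to treat the 12% and 20%, which the article labels prevalence, as incidence. The balance between groups would not alter incidence within either group in any case.

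**Conclusion.** The concern holds as a matter of stated scope. The article claims a property, in the Abstract, Methods and Discussion, that its own account of selection does not provide. The limitation acknowledges the selection but leaves the claims as they are.

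No numerical size can be attached. The direction and amount by which stability-selected women differ in OP incidence cannot be derived from the document. That selection could affect incidence within each group, which is why group-specific figures should be presented as belonging to the cohort.

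A reader might go further and infer that the comparison by dyslipidemia status is invalid, or that all the women form a mere convenience sample. The document supports neither. It says nothing to show that selection operated differently by dyslipidemia status, and it names regional and cooperation criteria that make purposive the fairer description. The verdict assumes only that the selection statements in the Discussion describe what will be done.

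**What to change.** Change the wording in three places and state the scope once:

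- In the Abstract, in Study design and settings and in the Discussion, replace *representative* and *population-based* with *non-randomly (purposively) selected women from hospitals and communities in three regions*.
- In the Discussion, remove the claim of effective extrapolation, or qualify it with the article's own limitation.
- State that conclusions rest on the within-cohort association between dyslipidemia and OP, and that OP incidence in each group is cohort incidence and not an estimate for Chinese postmenopausal women.

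If the full protocol does contain a sampling frame and selection method that would support a broader claim, describe it and limit the claim to what it supports.

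The cost is a narrower stated scope. Recruitment, follow-up, measurements, analysis, sample size and power do not change.

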**Figure 1 F1:**
[figure not shown]
Flow diagram of the study.

### Ethics and registration

This study was approved by the medical ethics committee of the Wangjing Hospital, China Academy of Chinese Medical Sciences (approval number: WJEC-KT-2021-040-P002) on 31 August 2021 and registered in the Chinese Clinical Trial Registry (approval number: ChiCTR2100051370) on 21 October 2021. The participants will be told the purposes and trends of the research, and their rights will be emphasized; then they will be asked to sign an “informed consent form” in accordance with the Helsinki Declaration.

### Participants

Due to the potential impact of different socioeconomic conditions on population bone mass, participants in this study will be recruited in different regions of mainland China (namely, northern China, southern China, and central China) from October 2022 to May 2023. The aim is to avoid the potential bias caused by economic circumstances, education, work, and other factors.

The subjects will be enrolled according to the established eligibility criteria: (1) Post-menopausal women; (2) aged from 45 to 64 years old; (3) *T-*value of bone density measurement is >-2.5; and (4) the participants are willing to participate in the investigation study.

Restrictive exclusion criteria are defined as follows: (1) A fragility fracture is found in the enrolled female; (2) the population who suffers from mental illness or are unable to complete the study.

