### Outcomes of interest

The pre-specified outcomes will be observed in detail and the outcomes reflecting bone transition are described. The primary outcome is the incidence of OP. During the study period, the condition of normal bone mass, osteopenia, and fragility fracture for each female will be also identified every year. For the event of OP-related fracture, different sites, occurrence times, and the number of fractures are completely recorded.

The secondary outcomes are radiographic BMD assessment and serum marker test. The blood indexes aim to reveal the dynamic changes in calcium and phosphorus metabolism, osteogenesis, and osteoclast function. Also, the recognized scales such as the health question scale, and specific relevant TCM syndrome differentiation scale will be investigated.

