### Questionnaire information

Face-to-face structured interviews will be done with a well-designed questionnaire by trained interviewers. The questionnaire will be used to collect information on the five collected domains. The aspects include: (1) general demographic information; (2) lifestyle and dietary behavior; (3) health status, comorbidities, and medication-taking condition; (4) recognized scales measuring osteoporosis risk, physical activity or quality of life; and (5) characteristics of TCM syndromes.

All the subjects with the researchers will complete the questionnaires at baseline and follow-up phase. Then, a complete post-enumeration check of the questionnaires will be performed.

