### BMD measurement

The BMD values can be measured at multiple skeletal sites using the accepted dual-energy x-ray absorptiometry (DXA) scanner manufactured by Hologic Inc. In the absolute BMD measurement of the human body, it is necessary to record the information of the lumbar spine, both hips, and the distal one-third of the radius site. In addition, the total *T-*value and the *T-*value of each site will be reported separately. Definitions of osteopenia and OP are in accordance with WHO standards on BMD measurement.

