### Sample size calculation

We calculated that a minimum sample size of 1,100 (550 DL and 550 non-DL) women are required to demonstrate an 8% difference in the prevalence of OP between DL and non-DL participants (14). The assumes are as follows: best-estimate OP prevalence of 12% among non-DL women and 20% among DL women; 5% level of significance; 90% power for a two-sided test. Furthermore, we considered a 20% dropout rate and finally calculated the sample size.

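### The entry criteria do not exclude women with an earlier osteoporosis diagnosis or bone-active treatment whose T-value is now above -2.5, so known cases can enter the risk set for incident osteoporosis

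*Protocol article*

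**What the plan says.** The Participants section gives a numbered list that it presents as the established criteria. There are four inclusions: postmenopausal, aged 45 to 64, a bone-density criterion ("value of bone density measurement is >-2.5") and willingness to take part. There are two exclusions: "Restrictive exclusion criteria are defined as follows: (1) A fragility fracture is found in the enrolled female", and "the population who suffers from mental illness or are unable to complete the study". Neither list refers to an earlier OP diagnosis or to current or past treatment acting on bone.

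Under Outcomes of interest, "The primary outcome is the incidence of OP". Study design and settings says "Each participant will be visited continuously once every year with a minimum follow-up of 3 years to track incidences of OP". The BMD measurement section fixes how a case is recognised: "Definitions of osteopenia and OP are in accordance with WHO standards on BMD measurement".

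The questionnaire, completed at baseline and follow-up, covers "health status, comorbidities, and medication-taking condition". No section uses these data to decide eligibility or membership of the at-risk set.

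**The concern.** An incidence needs a denominator of women who do not already have the disease. The T-value and fracture criteria show that the authors meant to remove existing disease, but a single current measurement cannot show disease that was diagnosed earlier and has since been treated to above the threshold.

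Followed as written, the plan can misclassify such a woman in two ways. If she falls to -2.5 or below during follow-up, a recurrence is counted as a first occurrence. If treatment holds her above -2.5, a known case is counted as a woman who stayed free of OP. Either way, the reported incidence is no longer purely that of new disease. If these women are spread unevenly between the DL and non-DL groups, or convert at different rates in the two groups, the comparison of the groups is distorted as well.

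**Working it through.** **Inputs from the document.** Planned OP rates come from Sample size calculation: "best-estimate OP prevalence of 12% among non-DL women and 20% among DL women", a difference of 8 points. The same section gives two-sided 5% significance, 90% power, 20% dropout and 550 women per group. Follow-up program expects less than 10% loss.

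**Inputs assumed.** The document does not give the share f of enrolled women with an earlier diagnosis or treatment, or the proportion r of them who fall to -2.5 or below during follow-up. The illustration takes f = 3% (non-DL) and 8% (DL), with r = 40% or 2%.

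**Step 1. The plan's own figure.** The pooled-variance formula without continuity correction, with mean rate 0.16, is

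n = [1.96 × √(2 × 0.16 × 0.84) + 1.282 × √(0.12 × 0.88 + 0.20 × 0.80)]² / 0.08² = (1.016 + 0.660)² / 0.0064, which rounds up to 440 per group.

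440 / 0.80 = 550 per group, or 1,100 in total. The stated figure reproduces exactly, and this point does not challenge it.

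**Step 2. Who passes the criteria.** Take a postmenopausal woman aged 45 to 64 and willing to join, with OP diagnosed earlier, bone-active treatment, no fragility fracture, no mental illness, able to complete the study, and a T-value now above -2.5. She meets all four inclusions and neither exclusion.

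**Step 3. Spurious difference when DL has no effect.** Let the risk for all other women be 12% in both groups. The observed risk in a group is (1 - f) × 0.12 + f × r.

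- r = 40%: non-DL 0.97 × 0.12 + 0.03 × 0.40 = 12.84%; DL 0.92 × 0.12 + 0.08 × 0.40 = 14.24%. The difference is +1.4 points, and 1.4 / 8 is about 18% of the planned effect.
- r = 2%: non-DL 0.97 × 0.12 + 0.03 × 0.02 = 11.70%; DL 0.92 × 0.12 + 0.08 × 0.02 = 11.20%. The difference is -0.5 points.

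With the same r in both groups, the difference reduces to (f in DL - f in non-DL) × (r - 0.12). It is zero when the shares are equal, and its sign depends on whether r is above or below 12%. With equal shares but unequal conversion it is f × (r in DL - r in non-DL). For example, f = 5% with 40% against 2% gives 0.05 × 0.38 = 1.9 points, in a direction that the document does not determine.

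**Step 4. Power with the women left in.** With 440 evaluable women per group and the planned 12% and 20% in the others, the results for assumed f of 1, 2, 5 and 10% are:

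- same share in both groups, none ever registering as a case: 89.7, 89.4, 88.2 and 86.2%;
- same share in both groups, all counted as new cases: 88.2, 86.3, 80.3 and 70.1%;
- present only in the DL group, none registering as a case: 88.7, 87.2, 81.9 and 70.3%.

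These are assumed extremes of classification, not expected values.

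**Step 5. Cost of taking them out.** With the 3% and 8% shares, 440 per group becomes 440 × 0.97 = 427 and 440 × 0.92 = 405. Power at 12% against 20% is then about 88%. If loss is 10%, the upper end of what Follow-up program expects, the numbers are 550 × 0.90 × 0.97 = 480 and 550 × 0.90 × 0.92 = 455. Both exceed 440, and power is about 92%.

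**The case against.** The strongest reply is that the risk set agrees with the protocol's own definition. OP is defined by BMD under the WHO standard, so a woman above -2.5 does not have OP at baseline on that definition, and the criteria also remove fragility fracture. This narrows the point: untreated densitometric OP and fractured women are already excluded, and only previously diagnosed or treated women now above the threshold remain. It does not remove the point, because a threshold crossing in such a woman is a return of known disease and not a first occurrence.

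Second, medication and comorbidities are recorded, medication use is confirmed every year, and adjusted models are planned. Recording makes the remedy easy, but the Statistical analysis section names no covariates, and adjustment cannot turn a recurrence into a new case. An analysis-set rule might sit in an analysis plan that is not shown. The entry criteria, however, are stated here as the established list, and the point is about what that list admits.

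Third, a reader might infer that such women certainly enter, or that the DL comparison is shown to be biased because recruitment runs partly through hospitals. The document supports neither reading. It shows only that they can enter. Nothing in it says that DL women come more often from hospitals or are diagnosed or treated more often. With equal shares and equal conversion there is no spurious difference under the null.

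A reader might also extend the point to glucocorticoid users and women with secondary causes of bone loss. Those women are not existing cases merely on that ground. They raise a question of confounding, which is a different matter.

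**Conclusion.** The point holds in a limited form: the stated entry rule lets women with known, previously diagnosed or treated OP into the risk set for incident OP. Their number, and the direction of any bias in the DL comparison, are unknown from the document.

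The +1.4 and -0.5 points rest entirely on the assumed 3% and 8% shares and the assumed conversion rates. Both are well below the planned 8 points. Because the sign can go either way, the bias cannot be dismissed as conservative. Power falls to about 70% only with a 10% share combined with an extreme assumption about classification or about the split between groups. The sample size of 1,100 stands. This is a cheap improvement, not a demonstrated flaw in the primary comparison.

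**What to change.** Add one sentence defining the primary at-risk set: women who at baseline have no earlier OP diagnosis and no current or recent bone-active treatment, with the treatments and the meaning of recent specified in advance. Report the unrestricted cohort as a sensitivity analysis, and give the number of women set aside in each DL group so that the share, now unknown, becomes visible.

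The rule can be an entry criterion or, if enrolment is complete, a restriction of the analysis set based on the baseline questionnaire. Confirm first that the questionnaire asks about an earlier OP diagnosis; the article names health status, comorbidities and medication but not this item.

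The cost is slightly fewer women in the primary set. If the rule is applied at entry, the target stays 1,100, and for assumed shares of 1, 2, 5 and 10% about 1,112, 1,123, 1,158 and 1,223 otherwise eligible women would need to be approached (1,100 / (1 - f)). If it is applied after enrolment, the loss of power is the small one shown in the working.
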